#### Statistical software and reproducibility

2.8.8

All analyses will be conducted using R (version 4.3.0 or later) and Python (version 3.8 or later) with specific packages documented for reproducibility. Version control using Git will track all analysis codes. Computational notebooks (R Markdown and Jupyter) will provide transparent documentation of analytical decisions and results.

Statistical significance will be set at α = 0.05 for primary analyses, with appropriate corrections for multiple testing. Confidence intervals (95%) will be reported along with p-values to provide the effect size context. Sample size considerations were based on effect sizes from published insomnia studies and power analyses of machine-learning applications.

### Sample size and power considerations

2.9

Participant recruitment for this deep phenotyping study has been completed in accordance with the original protocol design. The study employed a rolling, observational recruitment framework, with the goal of achieving a sample size sufficient for robust multimodal analyses across clinical, behavioral, physiological, and digital domains. Based on feasibility and methodological considerations, the protocol specified minimum recruitment targets of approximately 330 participants in total, including at least 240 individuals with insomnia and at least 80 good-sleeper controls.

These targets were established to ensure statistical adequacy for the key analytic aims while maintaining the feasibility of comprehensive multimodal data collection. Power estimations at the design stage indicated that, under this allocation (unequal groups, α = 0.05), the study would achieve about 80% power to detect standardized mean differences of Cohen’s d ≈ 0.36, which represents a small-to-moderate and clinically meaningful effect commonly observed in sleep research. For correlational analyses involving continuous variables, a total sample of this magnitude provides approximately 80% power to detect correlations of r ≈ 0.15–0.16, assuming complete data pairs. For predictive analyses, a balanced-class equivalent sample of this scale would permit area under the curve (AUC) estimates around 0.70 with a standard error of approximately 0.03, corresponding to a 95% confidence interval of roughly ±0.06. These calculations reflect the expected precision and effect sizes typical of multimodal insomnia research rather than formal hypothesis testing for a single endpoint.

In practice, 338 participants were enrolled, comprising 249 individuals with insomnia and 89 good-sleeper controls, consistent with the predefined recruitment objectives. Within the insomnia group, severity distribution according to the Insomnia Severity Index (ISI) was mild = 130, moderate = 101, severe = 18. Analyses involving ISI will therefore treat severity as a continuous variable or use pooled strata where appropriate, given limited sample sizes in the extreme categories. The analytic plan includes standard measures to ensure that statistical modeling remains commensurate with the available data, including internal cross-validation and regularization to reduce overfitting in multivariate and machine-learning models.

Overall, the final achieved sample meets and slightly exceeds the planned minimum targets, providing adequate statistical precision and methodological robustness for the multimodal analyses described in this protocol.

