### Participants

2.2

This study will recruit two parallel cohorts, an insomnia group and a normal sleeper control group. The inclusion and exclusion criteria for each cohort will be carefully defined to ensure a homogeneous sample and minimize confounding factors.

Participants in the insomnia group will be adults aged 19–70 years who report experiencing subjective insomnia symptoms, such as difficulty initiating sleep, difficulty maintaining sleep, or early morning awakenings, for at least three nights per week over the preceding three months. A score of 15 or higher on the Insomnia Severity Index (ISI) will be required to ensure that participants experience at least a moderate level of insomnia (21).

The normal sleeper control group will also consist of adults aged 19–70 years. To be included, these individuals must report experiencing insomnia symptoms less than three times per month, have an ISI score of less than 8, and report an average sleep duration of six hours or more per night over the preceding three months. Controls have no history of chronic insomnia or any major psychiatric illness and will also be required to comply with all the study procedures.

All participants in both groups are required to be willing to comply with all the study procedures, including the use of wearable devices and smartphone applications.

To minimize the influence of confounding factors, individuals meeting any of the following criteria were excluded from participation in either group: evidence of other primary sleep disorders such as untreated sleep apnea, narcolepsy, or other sleep-related breathing disorders; a current diagnosis of a major psychiatric disorder, including major depression, bipolar disorder, or schizophrenia, or a severe substance use disorder; the presence of cognitive impairment or a neurological disorder that could preclude valid self-report or compliance; participation in shift work or maintenance of an irregular sleep schedule within the past three months; and lack of access to a compatible smartphone or unwillingness to use the study’s smartphone application. The current use of hypnotic medications or supplements that have a significant effect on sleep was also an exclusion criterion.

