#### Sleep-related assessments

2.4.1

The sleep assessment battery was designed to capture multiple dimensions of sleep health and related behaviors that contribute to the pathophysiology of insomnia.

*Primary sleep measures*: The Insomnia Severity Index (ISI) (21, 22) serves as the primary outcome measure for insomnia severity, administered at screening for group allocation (≥15 for the insomnia group; <8 for controls) and weekly thereafter via the SOMDAY application. The Pittsburgh Sleep Quality Index (PSQI) (23, 24) assesses global sleep quality over the past month, whereas the Sleep Health Index (SHI) (25) provides a comprehensive measure of sleep health across multiple domains.

*Sleep disorder screening*: The Epworth Sleepiness Scale (ESS) (26, 27) measures daytime sleepiness, the Berlin Questionnaire (BQ) (28, 29) screens for obstructive sleep apnea risk, and the International Restless Legs Syndrome Rating Scale (IRLS) (30) assesses RLS (Restless Legs Syndrome) symptom severity.

*Sleep-related behaviors and cognitions*: Several instruments assess factors known to perpetuate insomnia. The Sleep Hygiene and Practices Scale (SHPS) (31, 32) evaluates sleep hygiene behaviors, whereas the Dysfunctional Beliefs and Attitudes about Sleep-16 (DBAS-16) (33) measures maladaptive sleep-related cognitions. The Morningness-Eveningness Questionnaire (MEQ) (34, 35) determines chronotype, Bedtime Procrastination Scale (BPS) (36) assesses bedtime delay behaviors, and Ford Insomnia Response to Stress Test (FIRST) (37) measures vulnerability to stress-induced sleep disturbance.

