##### Insomnia Severity Index

2.4.1.1

The ISI is a seven-item self-reported scale rated from 0 to 4 per item, with a total score ranging from 0 to 28. This scale assesses difficulty in initiating and maintaining sleep, early morning awakening, satisfaction with sleep, daytime functional impairment, impact on quality of life as observed by others, and worry about sleep problems. Scores of 0–7 indicate no clinically significant insomnia, 8–14 indicate mild insomnia, 15–21 indicate moderate clinical insomnia, and 22–28 indicate severe clinical insomnia. The ISI demonstrates a Cronbach’s α of 0.83, which reflects good internal consistency across diverse populations (38). In this study, the ISI is administered at screening to allocate participants (ISI ≥ 15 for the insomnia group; ISI < 8 for the control group), and thereafter, it was administered weekly to evaluate the subjective insomnia severity.

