Several limitations may affect the interpretation and generalizability of the findings of this deep phenotyping protocol. This study has limitations related to its single-center setting and sample composition. While a single-site setting allows for rigorous standardization of data collection, instrumentation, and participant monitoring—crucial for integrating multimodal measures such as digital phenotyping, neuroimaging, and genomics—it inherently limits representativeness. Convenience sampling and hospital-based recruitment may introduce selection bias, potentially overrepresenting individuals with more severe insomnia symptoms. Future multicenter and cross-cultural studies including more heterogeneous clinical populations will be necessary to validate and extend the generalizability of these findings. This observational design precludes causal inferences regarding the relationships between the identified phenotypes and clinical outcomes. The 4-week monitoring period may not capture the long-term trajectories or seasonal variations relevant to comprehensive phenotyping. Consumer-grade wearable devices have inherent accuracy limitations compared with PSG, particularly in the classification of sleep stages. Despite these constraints, wearable-based monitoring offers important advantages in terms of ecological validity, enabling the assessment of habitual sleep patterns and minimizing the first-night effect commonly observed in laboratory sleep studies. To address this limitation, future studies would benefit from incorporating a validation sub-study directly comparing Fitbit-derived sleep measures with simultaneous PSG recordings.

The wearable data in this study were sampled at 5-minute intervals and derived from photoplethysmography rather than ECG, which limits the temporal resolution and accuracy of short term autonomic measurements. Nevertheless, this approach provides valuable insight into long term physiological patterns in real world settings, and future studies using research grade devices with raw PPG or ECG signals could further improve measurement precision.

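### The insomnia group is defined by ISI ≥15, yet 130 of its 249 members are reported in the protocol's own mild band (8–14), and nothing in the article reconciles the two

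*Protocol article*

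**What the plan says.** **The rule.** Section 2.2 (Participants) says of the insomnia group: "A score of 15 or higher on the Insomnia Severity Index (ISI) will be required". The reason given there is to secure at least moderate insomnia. Section 2.4.1 says the ISI is "administered at screening for group allocation (≥15 for the insomnia group; <8 for controls", and section 2.4.1.1 repeats it: "ISI ≥ 15 for the insomnia group; ISI < 8 for the control group".

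**The bands.** Section 2.4.1.1 states that scores of "8–14 indicate mild insomnia, 15–21 indicate moderate clinical insomnia, and 22–28 indicate severe clinical insomnia". Table 1 gives the same cut-points.

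**The enrolled sample.** Section 2.9 reports that "338 participants were enrolled, comprising 249 individuals with insomnia and 89 good-sleeper controls", and that in the insomnia group "severity distribution according to the Insomnia Severity Index (ISI) was mild = 130, moderate = 101, severe = 18". It describes recruitment as completed in line with the protocol's design and objectives, against minimum targets of 240 with insomnia and 80 controls. It concludes that "the final achieved sample meets and slightly exceeds the planned minimum targets".

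**The only handling offered.** Section 2.9 says ISI severity will be analysed as a continuous variable or in pooled strata, because the extreme categories are small.

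**The concern.** Under the stated rule a score of 8–14 belongs to neither group: too low for a case, too high for a control. Yet the mild band is the largest of the three reported among the cases. The article mentions no lower threshold, no change to the rule, no deviations and no separate time point for the counts. Treating severity as continuous or pooling strata deals with sparse categories; it does not address eligibility.

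The case definition carries all three objectives in section 2.8: group differences, subtypes and prediction. With cases at 15 or above and controls at 7 or below, the groups are at least 15 − 7 = 8 points apart. With cases from 8 upward, the two groups occupy adjacent bands. Those are different contrasts, and an effect size or AUC means something different in each. A reader of section 2.2 would take the results to describe moderate-to-severe insomnia; a reader of section 2.9 would see a cohort that is about half mild. If the choice is left until results are seen, the case definition becomes data-dependent.

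**Working it through.** **1. Do the counts cover the whole group?** (section 2.9)
- 130 + 101 + 18 = 249, and 249 + 89 = 338. Every insomnia participant is in one of the three bands, and none is reported below 8.
- Mild: 130/249 = 52.2%. Moderate or severe: 101 + 18 = 119.
- Against the insomnia minimum: 119/240 = 49.6%, a shortfall of 240 − 119 = 121.

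**2. Group comparison.** Inputs from section 2.9: α = 0.05, d = 0.36, about 80% power. Sidedness is not stated. Two-sided reproduces the figure (one-sided would give 87.4% for 240 versus 80), so two-sided is used.

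Formulas, with se = √(1/n₁ + 1/n₂): power ≈ Φ(d/se − 1.960); detectable d at 80% power = 2.8016 × se.

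| Insomnia vs controls | se | Power at d = 0.36, normal (noncentral t) | Detectable d |
|---|---|---|---|
| 240 vs 80 (planned) | 0.1291 | 79.6% (79.4%) | 0.362 |
| 249 vs 89 (as enrolled) | 0.1235 | 83.0% (82.8%) | 0.346 |
| 119 vs 89 (ISI ≥15 bands only) | 0.1401 | 72.9% (72.5%) | 0.393 |

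The planned row reproduces the article's figure.

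**3. Correlation in the total sample.** Detectable r at 80% power = tanh(2.8016/√(n − 3)).
- n = 320: 0.156; n = 330: 0.154; n = 338: 0.152. These match the stated 0.15–0.16.
- n = 119 + 89 = 208: 0.193. At this size, power at r = 0.16 is about 64%.

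**4. The possible explanations, side by side**
- *ISI ≥8 was the rule applied.* Sections 2.2, 2.4.1 and 2.4.1.1 are wrong. The target and power statements hold, for a population that is at least mild.
- *ISI ≥15 was the rule and the counts are screening scores.* The 130 are deviations, and the insomnia target is missed by 121 for the defined population.
- *ISI ≥15 was the rule and the counts come from another ISI.* Table 1 also lists baseline, weekly and week-4 administrations. The rule and the target claim could then both stand, but the article omits the time point that would show it.

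Under each explanation, something printed is either wrong or materially incomplete.

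**The case against.** The strongest reply is that the article does not date the severity counts. Allocation used the screening ISI, and the scale was given again later, so some or all of the 130 may have scored 15 or more at screening. This stands. That nobody in the group is reported below 8 makes a late time point less likely, but does not exclude it. A reader might therefore infer that over half the cohort is ineligible and that the eligible number is 119; the documents support this only if the counts are screening scores.

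A reader might also infer that the power statement is false. It is not: it is a design-stage figure, it reproduces, and power is higher as enrolled. Section 2.9 also says that these figures describe expected precision and do not plan a formal test of one endpoint. The loss appears only in the restricted set and is moderate.

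The limitation in section 3 about "potentially overrepresenting individuals with more severe insomnia symptoms" might seem to clash with a cohort that is 52% mild. It is hedged and concerns hospital-based sampling relative to a wider population. With no reference distribution given, nothing shows it to be wrong.

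Likewise, the documents do not call scores of 8–14 sub-threshold, and they give no figure for any dilution of group differences. Finally, the severity split is disclosed openly, and clustering uses digital features, not ISI bands. That tempers any charge of concealment, but leaves the conflict over eligibility unresolved.

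**Conclusion.** The contradiction is real and needs correcting before analysis. The rule is stated three times and the bands twice, so a single slip of the pen is an unlikely explanation. The 130 of 249 (52%) in the mild band cannot be squared with the ISI ≥15 rule and the claims of adherence and target attainment unless the counts are not screening scores, which the article does not say.

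The consequence is chiefly about who the cases are and whether the insomnia minimum was reached (119 or 249 against 240). The effect on power is secondary and conditional: about 83% if all 249 form the defined group, about 72.5% with a detectable d of about 0.39 if only 119 do. The corresponding total-sample correlation is about 0.19 instead of 0.15–0.16. These figures assume two-sided α = 0.05, complete data and no covariate adjustment; the restricted ones further assume that the reported bands are screening scores.

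**What to change.** Before analysis, state two facts: the ISI threshold actually applied at screening, and the assessment from which the severity counts were taken. Then:

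- **If ISI ≥8 was applied:** correct sections 2.2, 2.4.1 and 2.4.1.1 and describe the cohort as at least mild. The power figures can stay (about 83% at d = 0.36 for 249 versus 89).
- **If ISI ≥15 was applied and the counts are screening scores:** report the 130 as deviations, use the eligible set (119 versus 89) for the primary comparisons, and keep all 249 as a secondary set. Restate section 2.9: 119 against the minimum of 240, power about 72.5% at d = 0.36, detectable d about 0.39, detectable total-sample r about 0.19.
- **If the counts come from a later ISI:** say so and give the screening distribution.

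The cost is a text correction and, in the second case, one additional analysis set. No new data are needed. The downside is a less favourable stated power if the ISI ≥15 set is used.

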## Discussion

3

This protocol presents a comprehensive and multimodal approach to the deep phenotyping of insomnia, a condition widely recognized for its clinical and etiological heterogeneity. Conventional assessment methods, often relying on demographic data analysis (61), self-reported subjective reports (62, 63), or single-night objective metrics, have shown limited reliability and poor concordance with perceived sleep quality (64, 65). Demographic data analyses and self-reported assessments (61–63) make it difficult to capture the complexity of insomnia. Therefore, our study aims to overcome these limitations by integrating data from clinical questionnaires, continuous digital phenotyping, functional neuroimaging, and genomics to comprehensively characterize the individual experiences of insomnia.

The primary strength and novelty of this protocol are its methodological integration. By combining continuous real-world data from wearables and smartphones with laboratory neurophysiological and biological measures, we can create a dataset of unprecedented depth and breadth. This approach intentionally bridges the gap between subjective, symptom-focused, and objective sleep measurement studies. Compared to single-night laboratory polysomnography, our wearable-based monitoring provides less detail on sleep architecture but offers far greater ecological validity by sampling multiple nights in the participant’s natural environment. This design enables the capture of the dynamic and fluctuating nature of insomnia, which static, single-time-point assessments often fail to do. However, this approach is not without its limitations. The sheer volume and complexity of multimodal data require sophisticated analytical techniques and careful management to avoid false discoveries. The intensive protocol may also impose a burden on participants, and the single-center design may limit the generalizability of the findings.

Implications of this deep phenotyping approach in sleep medicine are substantial. The primary object is to support a paradigm shift from undifferentiated care to personalized management. Tailoring insomnia treatments, such as cognitive behavioral therapy for insomnia (CBT-I) or pharmacotherapy, requires recognizing biologically distinct subtypes, including those characterized by physiological hyperarousal or circadian rhythm disruption (66–68).

More profoundly, the implications of this research approach extend beyond subtype discovery to both measurement and understanding of mental and sleep-related disorders. Continuous digital phenotyping replaces cross-sectional assessments with longitudinal measurements, enabling the development of predictive models that can forecast periods of heightened risk or detect early warning signs of relapse. Such models serve as the foundation for developing just-in-time adaptive interventions, where a digital platform can provide precise support when needed. Ultimately, this methodology aims to identify and validate novel digital biomarkers—objective, quantifiable indicators of the disease state derived from personal devices—which could substantially improve both clinical trials and routine patient monitoring, thereby contributing to precision sleep medicine. In conclusion, this protocol outlines a feasible and comprehensive strategy to characterize the complex phenotype of insomnia, with the potential to yield insights and tools that unidimensional approaches cannot provide.

Several limitations may affect the interpretation and generalizability of the findings of this deep phenotyping protocol. This study has limitations related to its single-center setting and sample composition. While a single-site setting allows for rigorous standardization of data collection, instrumentation, and participant monitoring—crucial for integrating multimodal measures such as digital phenotyping, neuroimaging, and genomics—it inherently limits representativeness. Convenience sampling and hospital-based recruitment may introduce selection bias, potentially overrepresenting individuals with more severe insomnia symptoms. Future multicenter and cross-cultural studies including more heterogeneous clinical populations will be necessary to validate and extend the generalizability of these findings. This observational design precludes causal inferences regarding the relationships between the identified phenotypes and clinical outcomes. The 4-week monitoring period may not capture the long-term trajectories or seasonal variations relevant to comprehensive phenotyping. Consumer-grade wearable devices have inherent accuracy limitations compared with PSG, particularly in the classification of sleep stages. Despite these constraints, wearable-based monitoring offers important advantages in terms of ecological validity, enabling the assessment of habitual sleep patterns and minimizing the first-night effect commonly observed in laboratory sleep studies. To address this limitation, future studies would benefit from incorporating a validation sub-study directly comparing Fitbit-derived sleep measures with simultaneous PSG recordings.

The wearable data in this study were sampled at 5-minute intervals and derived from photoplethysmography rather than ECG, which limits the temporal resolution and accuracy of short term autonomic measurements. Nevertheless, this approach provides valuable insight into long term physiological patterns in real world settings, and future studies using research grade devices with raw PPG or ECG signals could further improve measurement precision.

The genomic analyses in this study focused primarily on polygenic risk scores and candidate gene expression to establish a foundational molecular framework. However, the exclusion of epigenomic and proteomic biomarkers may limit the ability to capture dynamic molecular mechanisms underlying insomnia. Future studies incorporating multi-omics approaches, including DNA methylation and cytokine profiling, could enhance the biological depth and robustness of the phenotypic characterization. The fNIRS approach has limited spatial resolution compared to fMRI and focuses only on prefrontal cortex function. Although this configuration provides practical advantages in terms of ecological validity and participant comfort, it restricts the assessment of deeper or posterior brain regions, such as the thalamocortical circuits, that are relevant to the pathophysiology of insomnia. Future studies should consider applying complementary neuroimaging techniques, such as fMRI, to overcome these spatial constraints and achieve a more comprehensive understanding of the neurophysiological mechanisms underlying insomnia. The intensive digital phenotyping protocol may impose a significant participant burden, potentially affecting them over time, whereas technology literacy requirements may exclude certain demographic groups. The high-dimensional nature of multimodal data may increase the risk of overfitting in machine learning analyses. Although robust internal validation using nested cross-validation was implemented, the absence of independent external validation remains a limitation that should be addressed in future studies. Furthermore such high-dimensional, multimodal dataset increases the risk of multiple testing problems despite statistical corrections, and the sample size may limit the detection of rare phenotypic subtypes. The study setting differs from typical clinical environments, which may limit the direct translation to routine practice. The exclusion of major psychiatric disorders and restrictions to ages 19–70 years limit their applicability to key clinical populations.

Despite these limitations, this comprehensive deep phenotyping approach represents a significant methodological advancement that will inform future research and establish a foundational knowledge base regarding precision sleep medicine.
